## Abstract

**Background:**

Parkinson’s disease (PD) results from a loss of dopamine in the brain, leading to movement dysfunctions such as bradykinesia, postural instability, resting tremor and muscle rigidity. Furthermore, dopamine deficiency in PD has been shown to result in maladaptive plasticity of the primary motor cortex (M1). Progressive resistance training (PRT) is a popular intervention in PD that improves muscular strength and results in clinically significant improvements on the Unified Parkinson’s Disease Rating Scale (UPDRS). In separate studies, the application of anodal transcranial direct current stimulation (a-tDCS) to the M1 has been shown to improve motor function in PD; however, the combined use of tDCS and PRT has not been investigated.

**Methods/design:**

We propose a 6-week, double-blind randomised controlled trial combining M1 tDCS and PRT of the lower body in participants (*n* = 42) with moderate PD (Hoehn and Yahr scale score 2–4). Supervised lower body PRT combined with functional balance tasks will be performed three times per week with concurrent a-tDCS delivered at 2 mA for 20 minutes (a-tDCS group) or with sham tDCS (sham group). Control participants will receive standard care (control group). Outcome measures will include functional strength, gait speed and variability, balance, neurophysiological function at rest and during movement execution, and the UPDRS motor subscale, measured at baseline, 3 weeks (during), 6 weeks (post), and 9 weeks (retention). Ethical approval has been granted by the Deakin University Human Research Ethics Committee (project number 2015-014), and the trial has been registered with the Australian New Zealand Clinical Trials Registry (ACTRN12615001241527).

**Discussion:**

This will be the first randomised controlled trial to combine PRT and a-tDCS targeting balance and gait in people with PD. The study will elucidate the functional, clinical and neurophysiological outcomes of combined PRT and a-tDCS. It is hypothesised that combined PRT and a-tDCS will significantly improve lower limb strength, postural sway, gait speed and stride variability compared with PRT with sham tDCS. Further, we hypothesise that pre-frontal cortex activation during dual-task cognitive and gait/balance activities will be reduced, and that M1 excitability and inhibition will be augmented, following the combined PRT and a-tDCS intervention.

**Trial registration:**

Australian New Zealand Clinical Trials Registry ACTRN12615001241527. Registered on 12 November 2015.

## Background

Parkinson’s disease (PD) is a progressive neurodegenerative movement disorder characterised by depletion of dopamine in the substantia nigra, resulting in physical symptoms such as bradykinesia, postural instability, resting tremor and muscle rigidity. PD is the second most common neurodegenerative disorder [1], affecting 1 % of people older than 60 years of age [2], which is of particular concern as populations age. PD causes significant impairments in gait and balance, which are often unresolved by standard dopamine pharmacological treatment [3] and result in reduced quality of life and increased risk of falls [4].

There is growing evidence for the use of progressive resistance training (PRT) to improve gait and lower limb muscle strength in PD [5]. The inclusion of other functional tasks, such as balance training, in PRT programmes has also been shown to decrease postural sway, reduce the risk of falls, and improve quality of life [6]. Importantly, functional PRT programmes have been shown to induce neuroplastic changes in the primary motor cortex (M1) of both healthy individuals [7] and people with PD [8]. This is of particular interest, as maladaptive M1 plasticity in patients with PD has been linked to poorer outcomes in motor learning and movement control [9, 10]. Evidence derived from transcranial magnetic stimulation (TMS) studies has demonstrated that patients with PD present with increased cortical excitability and reduced inhibition at rest, which is evidenced by lower motor threshold, increased motor evoked potential (MEP) amplitude, reduced short-interval intra-cortical inhibition (SICI) [10] reduced silent period [11]. Furthermore, reduced intra-cortical facilitation and absence of MEP size increase during contraction suggests defective facilitatory cortical inputs, particularly for movement execution [12]. In addition, the absence of a putative neuroplastic response following paired associative stimulation [13, 14], as compared with healthy control subjects, suggests that the facilitation of M1 plasticity in patients with PD may play an important role in the restoration and maintenance of motor performance.

Transcranial direct current stimulation (tDCS) is a form of non-invasive brain stimulation that has been shown to modulate excitability of the M1 in a polarity-specific manner when applied for short periods (10–20 minutes). When anodal tDCS (a-tDCS) is applied to the M1, there is a transient increase (up to 90 minutes) in excitability and reduction SICI of underlying neurons [15], as well as widespread changes in activation of cortical and subcortical areas [16]. There is substantial evidence to suggest that the application of a-tDCS to the M1 results in improved motor function in healthy populations, including increased performance in skill and strength tasks [17, 18], and this may be especially true when tDCS is applied during concurrent motor practice or training [19].

The use of tDCS as an independent intervention in PD has produced promising results, with evidence for improved working memory and executive function [20, 21], reduced bradykinesia, and increased walking speed following tDCS [22]. Importantly, clinically significant improvements in the motor component of the Unified Parkinson’s Disease Rating Scale (UPDRS) have been reported following bilateral a-tDCS of the M1 [23]. A recent pilot study of eight participants reported for the first time that combined gait training and M1 a-tDCS showed promising improvements in walking and balance measurements, but the researchers in that study concluded that larger trials were required to produce definitive results [24].

Given the existing evidence for enhancements in neuroplasticity and motor performance following both PRT and tDCS as independent treatments, it is reasonable to conclude that the combination of these two interventions may further augment functional benefits in patients with PD. Indeed, a combination of a-tDCS and motor training appears to produce a compounding effect on motor performance and neurophysiological adaptations in healthy populations [25, 26] and stroke-affected individuals [27, 28]; however, the application of a-tDCS during PRT and balance training in PD is yet to be investigated.

## Methods/design

### Aims

The primary aim of this pilot study is to determine the effects of a 6-week lower limb balance and PRT intervention with concurrent a-tDCS on gait, balance, strength and UPDRS motor scores in patients with PD. In addition, we will investigate neurophysiological adaptations in M1 excitability and pre-frontal cortex (PFC) activation as potential underlying mechanisms. It is hypothesised that the combination of PRT and a-tDCS will produce favourable functional motor outcomes and neuroplasticity beyond the effects of PRT alone.

### Eligibility and recruitment

The recruitment, screening and randomisation process is shown in Fig. 1. Potential participants will be recruited on a voluntary basis with the assistance of the Australian Parkinson’s Disease Registry and neurology clinics within the Melbourne metropolitan area. All participants will provide written informed consent as well as written approval from their general practitioner before partaking in physical exercise. Prior to enrolment in the study, a series of screening questionnaires will be completed by telephone to determine eligibility.

**Fig. 1 Fig1:**
[figure not shown]
Flow diagram of recruitment, screening and randomisation process. *a-tDCS* anodal transcranial direct current stimulation

The following inclusion criteria will be applied:Diagnosed with PD by an independent neurologistModerate motor symptoms (score between 2 and 4 on the Hoehn and Yahr scale, as assessed by an independent neurologist and confirmed at initial assessment by a blinded researcher)Stable drug regime for the full duration of the study and the 6 weeks preceding the studySelf-reported history of one or more falls in the last 24 monthsNot currently undertaking a regular exercise programme

Potential participants will be excluded if they present with any of the following:Severe motor impairments or injuries that will impair the ability to perform lower limb PRT (confirmed at initial assessment by blinded researcher)Previously diagnosed neurological condition separate from PD (stroke, dementia, epilepsy)Metal implants in the head (i.e., deep brain stimulator or aneurysm clips), which are contraindicated with non-invasive brain stimulation techniques

### Randomisation and blinding

Once recruited, simple randomisation using a computerised sequence generator will be used to allocate participants to one of three study groups (a-tDCS, sham or control). Opaque envelopes will be used to conceal the group allocation, which will not be revealed until after all data have been analysed. A researcher who is otherwise removed from the study will program the tDCS machine before PRT sessions to ensure double-blinding of both researcher and participant. Participants allocated to the control group will be notified of their allocation and will be asked to attend assessment sessions only.

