### Sample size calculation and statistical analysis

Gait speed, static balance and UPDRS-III at T6 will serve as primary outcome measures, with all other assessments and time points serving as secondary outcome measures. Based on the effect size observed in a recent study using a-tDCS during walking exercise [24], it is estimated that 42 participants randomised equally to three groups will be needed. Fourteen participants in each intervention group (a-tDCS, sham, control) will provide at least 80 % power to detect a 10–15 % difference in gait speed and static balance (centre of pressure), assuming a 5 % significance level. In functional assessments, a 10–15 % difference equates to an increase of 5.2 points on the UPDRS-III, which indicates a moderate clinically important difference [61].

A two-way, repeated-measures, mixed-design analysis of variance with factors time (T0 vs. T3 vs. T6 vs. T9) and treatment (a-tDCS vs. sham vs. control) will be used to determine any effect of the intervention on balance, gait speed and measures of brain physiology. False discovery rate analysis will be applied to determine when and where significance is found. An alpha level of *P* < 0.05 will be set to determine significance.

Where possible, we will obtain endpoint measures from all withdrawals and will include all randomised subjects in the final analysis. For participants who are lost to follow-up, missing data will be handled with multiple imputation. As this approach makes an untestable assumption that data are missing at random (i.e., missing data can be predicted from the observed data) [62], we will perform sensitivity analysis to evaluate the effect of potential non-random attrition [63]. Sensitivity analyses will employ simulation and will test a range of scenarios assuming plausible arm-specific differences in outcomes for individuals who were lost to follow-up [64].

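### Simple randomisation does not guarantee the 14 per arm on which the stated power rests; with 42 participants an exact 14/14/14 split has a 1.9 % chance

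*Protocol article*

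**What the plan says.** Under Randomisation and blinding, the protocol article says that "simple randomisation using a computerised sequence generator will be used to allocate participants to one of three study groups". It then describes opaque envelopes for concealment and adds that control participants are told their allocation. It mentions no blocks, strata, minimisation or list of fixed composition, and neither does any other text shown. The flow diagram (Fig. 1) is not shown.

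Under Sample size calculation and statistical analysis it says that "it is estimated that 42 participants randomised equally to three groups will be needed", and continues: "Fourteen participants in each intervention group (a-tDCS, sham, control) will provide at least 80 % power". The target is "to detect a 10–15 % difference in gait speed and static balance (centre of pressure"), "assuming a 5 % significance level". The basis is given as "Based on the effect size observed in a recent study using a-tDCS during walking exercise", but no mean, standard deviation or standardised effect is stated.

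**The concern.** Simple randomisation gives each participant an independent one-in-three chance of each arm. The three arm sizes are then random, and only their total is fixed at 42. The power statement treats them as fixed at 14. The phrase about equal randomisation could mean equal probability alone, but the next sentence attaches the power to fourteen people in each named group, which is a realised size.

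The hypothesis compares active stimulation plus training with sham plus training, so that pair of arms matters most. If either arm is short, the comparison loses precision. The Discussion also concedes a reduced sample size while asserting that any clinically significant benefit would be detected statistically, and that assertion draws on the same calculation.

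**Working it through.** **Inputs.** From the protocol: N = 42, three arms, simple randomisation, 14 per arm, power of 80 % or more, 5 % significance. Assumed: equal probabilities of 1/3 and a two-sided test. Also assumed, because no standard deviation is given: a standardised difference d chosen so that 14 v 14 has 80 % power.

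**1. The plan's own figure.** The 80 % cannot be rebuilt from the document, because a 10–15 % difference has no power without a standard deviation. It can only be solved backwards.
- Normal approximation: d = √(2/14) × (1.960 + 0.842) = 1.06.
- Two-sample t-test (noncentral t, 26 degrees of freedom): d = 1.10.

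The value 1.10 is used below.

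**2. Chance of exact balance.** Under simple randomisation the arm sizes follow a multinomial distribution:

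P(14, 14, 14) = 42! / (14!)³ / 3⁴² = 0.0194, or 1.9 %.

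This needs no assumption about the effect.

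**3. How unequal the arms tend to be.** Summing the multinomial over all splits of 42:

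| Event | Probability |
|---|---|
| All three arms 13 or more | 17.5 % |
| Smallest of the three arms 11 or fewer | 59 % |
| Smallest of the three arms 10 or fewer | 37 % |
| Active or sham arm 11 or fewer | 41 % |
| Largest minus smallest arm 6 or more | 55 % |

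The expected smallest arm is 10.9 and the expected largest 17.2.

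**4. Effect on power, active v sham.** For arm sizes n₁ and n₂, the noncentrality parameter is d / √(1/n₁ + 1/n₂), with n₁ + n₂ − 2 degrees of freedom. At d = 1.10:

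| Split | Power |
|---|---|
| 14 v 14 | 80.0 % |
| 12 v 14 | 76.5 % |
| 11 v 14 | 74.4 % |
| 10 v 14 | 71.9 % |
| 11 v 11 | 69.0 % |

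Weighting every split by its probability:
- mean power is 78.0 %, with a 5th to 95th percentile range of 68 % to 86 %;
- power is below 80 % in 59 % of splits, below 75 % in 27 % and below 70 % in 8 %;
- power is above 80 % in 39 % of splits.

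The remaining 2 % or so is the exact 14 v 14 split. The figure of 59 % appears twice by coincidence: one is the chance that the smallest of three arms has 11 or fewer, the other the chance that power for one pair is below 80 %.

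**The case against.** The strongest reply is that planning power at the expected arm size is ordinary practice. Fourteen is the expected size under equal probabilities, so the two sections can be read together. The word simple may also be used loosely for an unstratified list held in envelopes. Either reading is possible, but the text supports neither directly: fourteen is stated as the number in each group, and no restriction is mentioned. The mismatch stands as something to clarify.

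Several further points stand and limit the finding.
- The average cost is about 2 percentage points of power (80 to 78), and the distribution has an upside as well. Active and sham together number at least the planned 28 in 57 % of splits.
- The smallest-arm figures include the control arm, which is not part of the active v sham comparison. For that pair alone, the chance of an arm with 11 or fewer is 41 %.
- The power figures use a back-solved effect and a two-sample t-test at one time point. The planned analysis is a mixed analysis of variance with three groups and four times.
- The article calls the trial a pilot and says its size was chosen for feasibility.

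A reader might infer more than this. One inference is that the two sections cannot both be true; they can, with probability 1.9 %. Another is that the trial's real power is below 80 % in 59 % of splits; the protocol claims 80 % as a minimum and gives no effect size, so this holds only at the assumed d. A third is that simple randomisation biases the comparison; it is a valid method and does not. A fourth is that leaving Hoehn and Yahr stage unstratified is an error. Eligibility does cover a "score between 2 and 4 on the Hoehn and Yahr scale", but the documents give no figure for added noise from stage, and the planned model includes baseline as a level of time.

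**Conclusion.** The concern holds as a mismatch between the stated allocation method and the stated basis for power. The arm sizes in the power statement are not a property of the design as described. The probabilities of unequal arms (1.9 % for exact balance, 59 % for a smallest arm of 11 or fewer) are exact, given 42 participants and equal probabilities. The power consequences (mean 78 %, below 75 % in 27 % of splits, above 80 % in 39 %) also depend on d = 1.10, a two-sided 5 % level and a two-sample t-test. The loss is modest on average, with a lower tail of 10 points or more. Validity is not in question. The matter is worth correcting because the trial is small and the correction is cheap.

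**What to change.** First establish how the list was made.

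- **If a restricted list is already in use**, correct the Randomisation and blinding section to say so and describe the restriction. Nothing else is needed.
- **If simple randomisation is in use and can be changed**, have someone independent of the trial team check the actual allocation counts and prepare a restricted list for the remaining envelopes. One form is a randomly permuted list of the places left in each arm up to 14, which brings the final split to 14/14/14 if no arm has already passed 14. Another is concealed blocks of varying size, which limit further drift but keep any imbalance already present. Report the method used before and after the change.
- **If simple randomisation is kept**, describe 14 per arm as the expected size only, and restate power over the likely arm sizes, as in the tables above.

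The number still to be allocated must come from the allocation record. The Trial status section accounts for 17 + 6 + 1 = 24 participants, but the six are described as in training. Controls attend assessments only, so controls in progress may not be counted, and 42 − 24 = 18 is not a safe figure for those remaining.

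The cost is a short amendment and, under the second option, a new list. The drawback of that option is somewhat more predictable allocation, because control participants are openly told their group. Keeping the list and any block sizes concealed from recruiting staff limits this. Stratification by Hoehn and Yahr stage is optional and not part of the correction.

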### Study overview

The study will run for a period of 9 weeks in total, including a 6-week intervention period and a 3-week follow-up. Participants will be randomly allocated to one of three groups:a-tDCS (required to perform PRT and balance training while receiving a-tDCS)Sham (required to perform PRT and balance training while receiving sham tDCS)Control (to receive standard care)

Exercise sessions will include PRT and balance training for a duration of approximately 40 minutes, and they will be completed on 3 non-consecutive days per week (18 sessions in total). Assessment sessions to evaluate outcome measures will take place at four time points: baseline (T0), mid-intervention at 3 weeks (T3), post-intervention at 6 weeks (T6) and retention at 9 weeks (T9). Assessment sessions will take approximately 3 h and will occur at the same time of day for each time point. All sessions will take place at the Deakin University Burwood campus in a specialised clinical exercise gym and laboratory facility. The control group will receive standard care for the duration of the study and will be required only to attend the assessment sessions. Figure 2 provides an overview of the study time frame and sessions. For the duration of the study, all participants will continue with their usual care and medications as prescribed by their physician. Any changes in medication status during the trial will be documented, and participants will be allowed to continue with the programme.

**Fig. 2 Fig2:**
[figure not shown]
Study timeline (**a**) and Standard Protocol Items: Recommendations for Interventional Trials (SPIRIT 2013) diagram (**b**) illustrate the schedule of enrolment, interventions and assessments. *fNIRS* functional near-infrared spectroscopy, *FTSTS* Five Times Sit-to-Stand Test, *PRT* progressive resistance training, *tDCS* transcranial direct current stimulation, *TMS* transcranial magnetic stimulation, *TUG* Timed Up and Go Test, *UPDRS* Unified Parkinson’s Disease Rating Scale

### Intervention

#### Strength and balance training

Participants will be required to attend PRT and balance training sessions at Deakin University Burwood campus three times per week, on non-consecutive days, for 6 weeks. All PRT exercises will be aimed at the lower body and will include the following: leg press performed on fixed pneumatic gym equipment (Air300; Keiser, Fresno, CA, USA) (see Fig. 3); sit to stand, progressing to body weight squat and addition of weight vest (5, 10 or 15 kg) (see Fig. 4); standing bilateral calf raise, progressing to unilateral calf raise and weighted vest (se Fig. 5); and seated unilateral dorsiflexion with free weight dumb-bell (see Fig. 6).

**Fig. 3 Fig3:**
[figure not shown]
Example of seated leg press

**Fig. 4 Fig4:**
[figure not shown]
Example of body weight squat

**Fig. 5 Fig5:**
[figure not shown]
Example of standing bilateral calf raise

**Fig. 6 Fig6:**
[figure not shown]
Example of unilateral dorsiflexion with free-weight dumb-bell

Participants will perform three sets of six to eight repetitions of each exercise, with resistance set at 70 % of their recorded single-repetition maximum (1RM). Repetition timing will be externally paced by an audible metronome consisting of 3-second concentric and 3-second eccentric contractions. For each exercise, resistance will be increased by 5 % when all sets can be completed with correct repetition timing and technique, as assessed by a trained exercise physiologist.

Between each set of exercises, participants will perform a functional balance task:Tandem stance, 4 × 15 seconds alternating the leading footSingle-leg stance, 4 × 15 seconds alternating the leading footTandem walk, 3 × 12 steps, heel to toe, in a straight lineHurdle walk, six laps of four hurdles (height = 30 cm)

Stance tasks will be performed with the assistance of the trainer if required and will be progressed by using unstable foam surfaces, duraDiscs (AOK Health, Newcastle, Australia), performing with the eyes closed, and receiving multi-directional perturbations. Walking tasks will be progressed by performing a concurrent dual task (naming colours, cities, countries, and so forth), adding 1-kg ankle weights, and being instructed to ‘pause’ and ‘reverse’ mid-task. Participants will advance to the next progression when the exercise physiologist deems that they can competently complete the task.

